### Process evaluation

We will conduct a mixed-methods, theory-driven process evaluation (PE), guided by the MRC’s 2008 framework [46] and Grant’s framework for process evaluations of cluster-randomised trials of complex interventions [47]. Our PE will be based on the underlying programme theory, namely the social cognitive theory, which views behaviour change and maintenance as a dynamic and reciprocal relationship determined by the person, their environment (their external social context) and their behaviour (their response to stimuli to achieve goals) [48]. Our PE aims to offer an exploration of ‘what worked, for whom and why’ in the implementation of the intervention [49]. Our specific objectives for the process evaluation are: (1) to describe the health system and service delivery context in which the intervention was delivered; (2) to examine recruitment processes, both at the cluster level (township hospital) and the individual level (patient consultations and prescriptions); (3) to report on intervention fidelity, both at the cluster level (training) and the individual level (provider delivery) and (4) to explore the responses to the intervention both at the cluster level (managers and providers) and the individual level (patients). Methods will include document review (e.g. recruitment records, meeting minutes), structured observation of trainings and consultations in the township hospital, questionnaires with township hospital family physicians, and interviews of more than 50 participants including six township hospital directors, 18 township hospital family physicians, 12 village doctors and 18 patients/their caregivers, all distributed between the intervention and control arms at a ratio of 2:1. We will also observe four training sessions in the intervention arm. In addition, we will conduct 12 observations of clinical consultations in the intervention arm and six in the control arm. The sample size of the qualitative study is purposively set according to our previous trial in Guangxi and will be adjusted during the study. Our qualitative methods will be guided by an interpretive description approach, which focusses on developing knowledge to inform clinical practice [32]. We will develop a sampling frame, purposively select participants for inclusion and collect data at 3, 6 and 12 months after the start of the intervention in four clusters in the intervention arm and two clusters in the control arm.

#### Analysis of process evaluation

We will analyse qualitative data from the PE using a framework analysis as described by Gale et al. to identify themes related to our study objectives [50]. This approach allows for the inductive discovery of new themes outside of our framework during analysis. We will transcribe and translate into English for all qualitative data, and do our analyses using NVivo 10 software. We will report our qualitative work following the Consolidated Criteria for Reporting Qualitative Research (COREQ) guidelines [51].

### Costing study

We will conduct an incremental cost-effectiveness analysis along with the trial. The primary outcome in this costing study is the cost per percentage point decrease in the APR (as defined in the ‘Outcomes’ section) in the intervention arm compared to the control arm. We will compare direct costs and outcomes of patients randomised to the intervention arm compared to the usual care arm over the 12-month time horizon of the trial. We will not discount costs and benefits due to the short period of the trial [52]. The perspective adopted for the analysis will be that of the healthcare provider.

#### Data collection

We will develop a questionnaire to collect data on the resources used to deliver the intervention, which we will aim to administer to the directors of all 34 township hospitals between the 9th and 12th months of the trial. We will collect information on: (1) average salaries, in renminbi (RMB), for each level of staff in their hospitals, (2) the duration of consultations, (3) the amount of time spent reviewing prescriptions in preparation for the prescribing peer-review meetings and (4) the frequency and duration of peer-review meetings and the staff involved in each process. We will ensure data quality by using double entry and by checking a random subset of the data.

#### Estimation of resource use and costs

Healthcare resource use includes patient visits to the health facility. We will include the cost of consultations, medications, medication reviews and subsidies. The total cost per patient will be calculated as the sum of the three elements: consultation, medication and medication reviews. We will calculate the total costs to the healthcare provider (township hospital) for the main analysis population (see the ‘Statistical analyses’ section) accounting for clustering and stratification [42].

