Provider side	1. Improved antibiotic stewardship programme: (a) Each township hospital will establish an antibiotic stewardship working team including the township hospital director and a senior physician. The team will decide local antibiotic policies (b) The antibiotic stewardship team will hold peer-review meetings on antibiotic use monthly throughout the intervention period and embedded within the routine meetings of family physicians. Before each peer-review meeting, the antibiotic stewardship team will hold an internal meeting to prepare prescription reviews. The results will be sent to individual family physicians through WeChat. Each physician will see their performance of appropriate antibiotic prescribing against the hospital average (c) The antibiotic stewardship team will organise monthly peer-review meetings in township hospitals to ensure: (1) clear targets are set for appropriate use, (2) specific feedback is provided to high prescribers on improvement, (3) adjusting assessments for individual physicians based on their performance and (4) recording monthly meeting memos (d) The research team will make monthly supervisory visits to intervention township hospitals. The supervisory visits will ensure: (1) adherence to the interventional activities, (2) feedback and an opportunity to answer questions, (3) meeting with the antibiotic stewardship team to strengthen leadership and their commitment to reduce antibiotic prescriptions 2. Operational guidelines to reduce antibiotic prescribing for ARIs will be used. The guidelines will include patient symptom-based diagnostic algorithms, when to/ not to use antibiotics, and when narrow-spectrum antibiotics are preferred. Based on Chinese guidelines, chest x-ray examinations will be recommended when symptoms indicate pneumonia but clinical signs are not severe, or if a patient makes a second visit with signs indicative of pneumonia. Key health education messages during consultations with patients are also included (a) Every family physician in the township hospitals will receive an operational guideline both in printed and app-based form (b) Village doctors will receive a brief operational guide regarding appropriate use of antibiotics and referral 3. Systematic training including a half-day training workshop run by a county-level hospital senior physician and the research team will be given to family physicians and village doctors. This will involve: (a) Lectures, case discussions, role plays and Q&As on appropriate antibiotic prescribing practices for RTIs based on operational guidelines. Every family physician in the township hospitals will receive a training booklet both in printed and WeChat-app form (b) Using the WeChat app to monitor antibiotic use based on monthly reports from the EMR system to facilitate physicians’ discussions (c) Communication skills training when consulting with patients and/or caregivers 4. Improved electronic prescription system in the EMR to help township hospital family physicians make appropriate decisions when treating patients for RTIs, involving: (a) Embedded modules to encourage appropriate antibiotic prescribing practice, such as pops-up of laboratory test checklists and recommended antibiotics to prescribe when prescribing (b) An alarm system will be implemented to alert the family physician about any patient who re-visits any hospital within 14 days or who has been admitted within 1 month for a respiratory infection or sepsis after their index visit. In this scenario, chest x-ray and blood profile examinations will be recommended and recorded	1. Currently most township hospitals have an existing antibiotic stewardship programme. However, the programmes are often not functioning because of specific targets and activities are planned/implemented. Township family physicians do already hold monthly administrative meetings, but no time is spent on antibiotic prescribing peer-review discussions 2. Township hospital family physicians will prescribe antibiotics according to existing national guide on use of antibiotics which are not specifically designed for primary care facilities, and rarely used. Most physicians prescribe based on their group practice and existing knowledge/practices. Any messages given by control-arm family physicians will be at their own discretion based on their existing practice and training 3. Township hospital family physicians receive relevant medical training before they obtain their qualifications, but only a few of them have opportunities to receive continuing training afterwards and these trainings are usually not specifically for respiratory infections or antibiotics use. We will not provide any training to control-arm family physicians 4. Township hospitals already have a similar electronic prescription system in the EMR, but there is no clinical decision module, alarm system or pop-ups for recommended and non-recommended antibiotics. We will not make this available for control-arm hospitals

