We will also collect and create the following secondary outcomes based on all eligible prescriptions. In our previous trial, we observed an increased use of Traditional Chinese Medicines, likely as alternatives to antibiotics, and a widespread misuse of glucocorticoids [17]. Thus, we will also measure: (6) the proportion containing any Traditional Chinese Medicines and (7) the proportion containing any glucocorticoids. Lastly, to evaluate if and how the intervention affects the mean cost of prescriptions issued to eligible patients we will also measure: (8) the average cost of a prescription, based on the cost of any medicines and (9) the average cost of a consultation (one per prescription), based on all costs including medicines, tests and the consultation.

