#### Primary and secondary outcomes

Following the baseline and the trial periods we will extract all eligible patient prescription data from the EMR for all township hospitals. The Prefecture Health Information Centre manages all EMR, and will provide encrypted and de-identified electronic prescription data (e.g. names, addresses and health insurance numbers will not be collected). We will then clean the data and enter it into a standard format database to store all outcome and covariate data (including diagnoses, medicines prescribed, medicine and consultation costs, plus patients’ age, sex, insurance status, date of visit, any related treatments, payment details and any re-visit or hospitalisation data). We will also collect relevant covariate data from all township hospitals, including family physicians’ age, sex, experience and qualification level, which we can be link to each prescription via unique prescriber IDs.

To allow us to exclude patient prescriptions from outcomes where the patients have excluding comorbidities, we will also record any comorbidities as per secondary diagnoses shown on prescriptions. We will also check medications listed on prescriptions to link them to possible diagnoses. For example, steroid inhalers with asthma or chronic obstructive pulmonary disease, anti-diabetic medications with diabetes, and anti-hypertensive medications with hypertension. The Prefecture Health Information Centre will use the encrypted personal health insurance numbers in each prescription to identify any long-term comorbidities recorded such as diabetes, hypertension, cardiovascular disease. We will also develop a list of keywords used locally in prescription diagnoses for respiratory infections (which are often symptom based), and will manually screen and code all prescriptions not containing an ICD-10 code of diagnosis.

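### The costing sum has no term for tests or imaging, so on its best-supported reading the cost per percentage point omits a cost that only the intervention arm's record system prompts

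*Protocol article*

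**What the plan says.** All references are to the protocol article.

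- **Costing study, Estimation of resource use and costs.** The included items are listed first: "We will include the cost of consultations, medications, medication reviews and subsidies". The rule follows: "The total cost per patient will be calculated as the sum of the three elements: consultation, medication and medication reviews". The list has four items and the sum has three. Tests and imaging are in neither, and subsidies are in the list only.
- **Costing study, Data collection.** The questionnaire to hospital directors asks for "average salaries, in renminbi (RMB), for each level of staff in their hospitals, (2) the duration of consultations", then for time spent preparing prescription reviews and for the frequency, length and staffing of peer-review meetings. It asks nothing about tests.
- **Costing study, opening paragraph.** Direct costs are compared between arms from the provider's perspective. The primary measure is cost per percentage point decrease in the APR.
- **Secondary outcomes.** Outcome 8 is "the average cost of a prescription, based on the cost of any medicines". Outcome 9 is "the average cost of a consultation (one per prescription), based on all costs including medicines, tests and the consultation".
- **Data collection and management, Primary and secondary outcomes.** The record extract is described as "including diagnoses, medicines prescribed, medicine and consultation costs" among other items.
- **Intervention, Table 2, provider side, item 4.** The intervention arm's electronic record gains pop-up laboratory checklists and an alarm for re-visits and admissions, of which the table says: "In this scenario, chest x-ray and blood profile examinations will be recommended and recorded". The control column says that its system has no decision module, alarm or pop-ups.

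**The concern.** The sum is written as complete, and its total is the cost input to the costing study's primary measure. The term consultation carries no definition there, and the rest of the article uses the word in more than one sense. On the sense that the costing section's own data collection supports, an item of direct provider cost is missing.

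An omission equal in both arms would cancel in the increment. This one is unlikely to be equal, because the prompts to test are part of the intervention and are withheld from control hospitals. The costing result could then look more favourable than the full direct cost would show. It could also differ from outcome 9, which does count tests, with no explanation in the plan.

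**Working it through.** No figure in the plan can be reproduced, because the article states no unit costs. The check is algebraic.

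**Notation, per patient.** C = the consultation itself (staff time), M = medicines, T = tests and imaging, R = medication reviews. A prefix d means intervention minus control. Subsidies are left out because neither their sign nor their size is given.

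**Target.** With each direct cost counted once, the total is C + M + T + R and the increment is dC + dM + dT + dR.

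**What the stated sum gives under each reading of consultation:**

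| Meaning of consultation | Support in the article | Stated sum | Error in increment |
|---|---|---|---|
| Staff time | Questionnaire collects salaries and duration; outcome 9 itself names the consultation as one part beside medicines and tests | C + M + R | -dT |
| All-in cost, as in outcome 9 | Secondary outcomes only; no cross-reference from the costing section | (C + M + T) + M + R = C + 2M + T + R | +dM |
| All visit costs except medicines | Compatible with the separate medicine and consultation costs in the record extract; stated nowhere | (C + T) + M + R | 0 |

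**Which reading is best supported.** Salary and duration are the inputs for costing staff time. They would not be needed if consultation meant the all-in figure of outcome 9. The first row is therefore the one to work with.

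**Effect on the ratio.** If the APR falls by D percentage points, the ratio is off by -dT/D. At the reduction assumed in the Sample size section, D = 15, this is -dT/15, or 1/15 = 0.067 RMB per patient per point for each RMB of dT. Purely for scale, an assumed dT of 2 to 6 RMB gives 2/15 = 0.13 to 6/15 = 0.40 RMB per patient per point.

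**When the sign would change.** A true net cost appears as a saving when dC + dM + dR is negative and smaller in size than dT: the other items save money, but less than the added tests cost.

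**Direction.** The intervention's prompts make dT > 0 plausible, and the increment is then understated. The article gives no data on test use in either arm, so this is an expectation and not a result.

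**The case against.** The strongest reply is that a journal article condenses the plan, that unit-cost definitions usually sit in a fuller document, and that consultation may simply mean everything at the visit except medicines. On that meaning nothing is lost or doubled. Outcome 9 will also report test-inclusive costs by arm, so test costs would not be hidden from readers.

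Part of this stands. The third reading is possible, and outcome 9 does give a partial safeguard. But the article does not leave the rule open: it states a closed sum of three elements. No section places tests within consultation, and outcome 9 lists tests beside the consultation. Outcome 9 is also a separate result and does not enter the cost-effectiveness ratio.

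A difference from outcome 9 is not in itself an error. The costing study uses a provider perspective and a staff-resource questionnaire, so the two figures need not match.

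A reader might infer something stronger: that the rule as written counts medicines twice, because outcome 9 defines consultation cost as including them. The documents do not support this. The costing section does not cite outcome 9, although it does cross-refer when it borrows the APR definition and the analysis population. It names consultation and medication as separate elements, and the record extract lists the two costs separately. Double counting is a risk of leaving the term undefined, not what the rule prescribes. Its direction is also unknown: the Secondary outcomes section reports increased use of Traditional Chinese Medicines in the previous trial, so dM could have either sign.

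**Conclusion.** The point holds as a gap in the costing rule. On the best-supported reading, the total cost per patient leaves out tests and imaging, and the increment is off by -dT. Because only the intervention arm has the prompts, the error is likely to differ by arm and understates the intervention's cost if tests rise. Double counting of medicines is a secondary risk from the undefined term. The subsidies mismatch is a plain inconsistency within the same paragraph.

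The conclusion rests on two assumptions: that consultation means staff time, and that the prompts change test use. The size in RMB cannot be given. It would also be too strong to say that the cost-effectiveness conclusion will reverse; that needs the condition shown in the working, and no figure in the article tells whether it is met. Only the costing study is affected, not the primary APR outcome, its analysis or the sample size. The wording should be settled before cost data are seen, so that the meaning of consultation cannot be chosen in the light of the result.

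**What to change.** In Estimation of resource use and costs, replace the three-element sum with: total cost per patient = consultation (staff time, salary times duration, excluding medicines and tests) + medicines + laboratory tests and imaging + medication reviews, each counted once. State in the same paragraph how subsidies enter, or remove them from the list. Add one sentence on how this total relates to outcomes 8 and 9.

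Using outcome 9 plus medication reviews would also count each item once, but it is not interchangeable with the sum above: it takes the recorded consultation cost in place of staff time. The sponsor should name one approach.

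The cost is a change of wording. Outcome 9 already needs test costs, so no new data source is required. The article does not say whether the records itemise them; if they hold only a visit total, tests would have to be obtained by subtracting the medicine and consultation charges. The downside is that the ratio may look less favourable to the intervention.

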#### Estimation of implementation costs

Implementation costs represent upfront costs and are estimated and reported separately, and will not be included in the cost-effectiveness analysis. However, policy-makers would need to consider these costs when deciding whether to implement the intervention at scale. We will calculate implementation costs for the software development, including the development of the WeChat app function and the EMR improvement. Then, for each cluster, we will calculate them as the sum of: the cost of a trainer to deliver training on appropriate use of antibiotics when treating acute RTIs, the cost of staff time to attend training, plus the costs of producing one handbook and one set of guidelines (used as information aids in consultations) per training attendee, and the educational videos (displayed in waiting areas) and posters (displayed around the hospital).

### Follow-up study

As with our previous trial [26] we will continue to follow-up both intervention and control-arm clusters for another 24 months after the trial ends to monitor the possible longer-term impact of the intervention. It will be at the discretion of individual township hospitals as to whether to continue the interventional activities after the trial has ended. We will investigate to what extent the township hospitals are willing to continue the interventional activities and the long-term influence on family physicians’ behaviors without any interventional efforts provided by the research team. All analyses will be fully pre-specified in the statistical analysis plan.

### Trial management

[name] from the University of Toronto and [name] from the Guangzhou Medical University will be the co-guarantees of the trial and will have full access to the trial dataset. We will establish a data management committee (DMC) led by external/independent members to safeguard the safety and privacy of the patients involved, and to ensure that all data is collected according to agreed ethical guidelines, properly stored and only used for research purposes. We will also form a trial steering committee (TSC) led by external members. We will organise teleconference meetings for both the DMC and TSC at the beginning of the study, and then every 6 months until the study completes. The committees may also meet on an ad-hoc basis should the need arise. During meetings we will discuss any protocol modifications. We will also establish a trial management unit (TMU) in Shaoguan, to manage the day-to-day activities of the trial, consisting of three research associates employed locally and two research associates from the University of Toronto.

